## 7 Assessments and schedule

### 7.1 Assessment items

#### 7.1.1 Screening assessments (items marked with \* are part of the standard initial work-up)

After obtaining informed consent and before registration, the principal or subinvestigator will perform the following assessments, observations and examinations to confirm eligibility.

To minimise subject burden, test results obtained before informed consent may be used if within acceptable time windows.

### **Subject background**

- Sex\*; age (at the time of informed consent)\*; use of anticoagulants (yes/no), drug name and dosage; medical history (diseases related to exclusion criteria); comorbidities.
- Height, weight, body mass index (BMI; calculated automatically) and body surface area (BSA; calculated automatically).
- World Health Organization (WHO) functional class.\*
- Resting 12-lead electrocardiogram\* and rhythm classification (sinus rhythm vs non-sinus rhythm). If non-sinus rhythm, document the type of baseline rhythm and heart rate.
- Pulmonary function tests (TLC measured value and % predicted; VC measured value and % predicted; FEV1 measured value and % predicted; FEV1/FVC%).\*
- Transthoracic echocardiography.\*
- Peak tricuspid regurgitation velocity; LVEF; cine images of parasternal long-axis and short-axis views and apical four-chamber view in B-mode and colour Doppler; and presence/absence of other echocardiographic findings suggestive of pulmonary hypertension (see Tables 3 and 4).
- Static chest radiography (e.g. conventional chest X-ray) (upright PA view is preferable).\*
- Blood tests\*:
  - - Complete blood count: white blood cell count, haemoglobin, platelet count.
  - - Biochemistry: total protein, albumin, blood urea nitrogen, creatinine, uric acid, total bilirubin, AST, ALT, LDH, C-reactive protein, sodium, potassium, chloride, estimated glomerular filtration rate.
  - - Coagulation test: D-dimer.
  - - Hormonal test: NT-proBNP.
- Presence/absence of organised thrombi on contrast-enhanced CT or pulmonary angiography. If performed between 180 days before registration and before the investigator's diagnosis of CTEPH/non-CTEPH, data from other institutions may be used.

#### **7.1.2 Dynamic chest radiography**

After obtaining a static chest radiograph (e.g. conventional chest X-ray) (supine anteroposterior view is recommended; alternatively upright posteroanterior view), dynamic chest radiography is acquired during breath-hold for 6–10 seconds (approximately 105 frames). For details of the imaging procedure, refer to “Section 5.2 Standards for acquiring dynamic chest radiography”.

The body position and projection during imaging and the times of entering and leaving the examination room will be recorded; examination time will be calculated from the time spent in the room. In facilities capable of measurement, radiation dose (DAP) will also be measured. The number of acquisitions including repeats due to inadequate breath-hold, etc., and the reasons for repeats will be recorded for each repeat. If imaging could not be performed for any reason, the reason for inability to acquire images will be recorded.

Dynamic chest radiography images with personal information masked will be submitted to the image interpretation committee.

#### **7.1.3 V/Q scintigraphy / SPECT-CT**

For ventilation scintigraphy, krypton-81m gas or technetium-99m aerosol (gas) will be used; for perfusion scintigraphy, technetium-99m macroaggregated human serum albumin (99mTc-MAA) will be used. V/Q scintigraphy is obtained by imaging the lungs with a gamma camera with detectors positioned outside the body. The presence/absence of regional ventilation–perfusion mismatch will be evaluated and recorded. Multi-direction planar images (including anterior and posterior views; only two views are acceptable), SPECT images, and (where available) CT images for fusion will be acquired. For details, refer to “section 5.3 Evaluation of pulmonary perfusion impairment in each of six lung regions on perfusion scintigraphy”.

Obtained images will have personal information masked and will be submitted to the image interpretation committee.

#### **7.1.4 Right heart catheterisation**

Right heart catheterisation will be performed under resting supine conditions to measure mean right atrial pressure, systolic/mean/diastolic pulmonary arterial pressure, mean pulmonary capillary wedge pressure, cardiac output (thermodilution is preferable), cardiac index and pulmonary vascular resistance (Wood units).

#### **7.1.5 Diagnosis**

After completion of the above examinations, the principal or subinvestigator will determine the diagnosis of CTEPH or non-CTEPH according to the diagnostic criteria below.

- CTEPH: all of the following are met:
  - 1) V/Q scintigraphy: segmental defects or multiple subsegmental defects on perfusion imaging.
  - 2) CT pulmonary angiography and/or catheter-based pulmonary angiography: findings of organised thrombi in the pulmonary arteries.
  - 3) Right heart catheterisation: pulmonary hypertension, defined as mPAP >20 mmHg at rest and pulmonary vascular resistance  $\geq$ 3 Wood units.
- Non-CTEPH: does not meet the criteria for CTEPH above.
  - a) A definitive diagnosis other than CTEPH is made (pulmonary hypertension clinical classification).

- b) Right heart catheterisation shows mPAP  $\leq 20$  mmHg (no pulmonary hypertension).
- c) An appropriate diagnosis cannot be made or appropriate images/data are not available, and the principal/subinvestigator judges the case to be inappropriate for evaluation in this trial.

Note: The definition of pulmonary hypertension is based on the 2022 ESC/ERS Guidelines, where pulmonary hypertension is defined as mPAP  $>20$  mmHg. Therefore, mPAP  $>20$  mmHg and pulmonary vascular resistance  $\geq 3$  Wood units are used in the diagnostic criterion in this protocol.

#### 7.1.6 Initial discrimination at the blinded core laboratory

Initial discrimination between CTEPH and non-CTEPH at the blinded core laboratory is not intended to be a definitive diagnosis, but rather to estimate the pre-test probability before specialised examinations. Accordingly, the judgement of whether the findings are suggestive of CTEPH is made comprehensively based on the initial work-up plus the pulmonary circulation analysis program (in the intervention group). If a regional perfusion defect is present on the pulmonary circulation analysis images, the case will be classified as CTEPH even if the initial work-up shows findings suggestive of non-CTEPH (e.g., left ventricular hypertrophy or pulmonary function abnormalities). For details of the reading procedure, refer to the SOP for image interpretation.

## 7.2 Schedule

The schedule of assessments is shown in Table 5.

**Table 5. Study schedule**

|                     | Informed consent | Screening | Registration | Examination    |                   |                | Allocation /image reconstruction | End of study (EoS)     |
|---------------------|------------------|-----------|--------------|----------------|-------------------|----------------|----------------------------------|------------------------|
| Visit window        | Day - 28 ~ Day 0 |           | Index Day 0  | Day 0 ~ Day 28 | Day - 28 ~ Day 42 | Day 0 ~ Day 42 |                                  | Within 7 days from EoS |
| Informed consent    | ○                |           |              |                |                   |                |                                  |                        |
| Eligibility         |                  |           | ○            |                |                   |                |                                  |                        |
| Enrollment          |                  |           | ○※1          |                |                   |                |                                  |                        |
| Patients background |                  | ○         |              |                |                   |                |                                  |                        |
| Height/weight       |                  | ○         |              |                |                   |                |                                  |                        |

|                                                 |  |     |  |     |     |     |   |   |
|-------------------------------------------------|--|-----|--|-----|-----|-----|---|---|
| WHO functional class                            |  | ○   |  |     |     |     |   |   |
| Blood test                                      |  | ○※2 |  |     |     |     |   |   |
| ECG                                             |  | ○※2 |  |     |     |     |   |   |
| Pulmonary function test                         |  | ○※2 |  |     |     |     |   |   |
| UCG                                             |  | ○※2 |  |     |     |     |   |   |
| Chest X-ray                                     |  | ○※2 |  |     |     |     |   |   |
| Dynamic chest radiography                       |  |     |  | ○※3 |     |     |   |   |
| V/Q scintigraphy / SPECT-CT                     |  |     |  | ○※3 |     |     |   |   |
| Right heart catheterisation                     |  |     |  |     | ○※2 |     |   |   |
| Final CTEPH/non-CTEPH diagnosis by investigator |  |     |  |     |     | ○※2 |   | ○ |
| Adverse events                                  |  |     |  | ○   |     |     |   | ○ |
| Malfunction                                     |  |     |  | ○   |     |     | ○ |   |

\* Items marked with an asterisk (\*) constitute the standard initial work-up information.

※1 Dynamic chest radiography should be performed within 28 days after registration; however, if performed between screening and registration, those images may be used.

※2 Right heart catheterisation should be performed within 28 days after registration; however, if performed within 180 days before registration, those data may be used.

EoT: End of testing; EoS: End of study.

## 8 Adverse events and malfunctions

### 8.1 Definition of adverse events

An “adverse event” refers to any unfavourable or unintended disease or disorder and its signs (including abnormal clinical laboratory values) that occurs in subjects, users or other

persons during use of the investigational device, regardless of whether a causal relationship with the investigational device is present. For events occurring in persons other than the subject, only those suspected to be influenced by use of the investigational device are included.

## **8.2 Evaluation and reporting of adverse events**

The intervention in this trial is acquisition of dynamic chest radiography. This is a non-invasive imaging examination with radiation exposure comparable to standard chest radiography (0.1–0.4 mSv) and does not exceed the scope of routine clinical practice. If an adverse event occurs in relation to the dynamic chest radiography procedure, the following will be recorded: adverse event name; the subject in whom it occurred; onset date; outcome; outcome date; severity; seriousness; causal relationship with the investigational device; measures taken regarding the investigational device; and treatments taken for the adverse event (including concomitant drugs and concomitant therapies).

If a serious adverse event occurs, the principal investigator will report it in accordance with Section 8.5 (Reporting procedures for serious adverse events and malfunctions).

### **1) Definition of serious adverse events**

Among adverse events, those that meet any of the following criteria are defined as serious adverse events:

- Death.
- A life-threatening event.
- Event requiring hospitalisation for treatment or prolongation of existing hospitalisation.
- Disability.
- Event that may result in disability.
- Event that is considered serious in accordance with the above items (1–5).
- Congenital disease or abnormality in subsequent generations.

### **2) Causal relationship between adverse events and the investigational device**

Causality between an adverse event and the investigational device will be classified as follows. “Related” refers to an event in which there is at least a reasonable possibility of a causal relationship between the adverse event and the investigational device and a causal relationship cannot be ruled out.

- Unrelated
- Related

### **3) Severity of adverse events**

If an adverse event occurs, severity will be recorded using the following Grade 1–5 scale:

- Grade 1: Mild – no symptoms or mild symptoms; no treatment required.
- Grade 2: Moderate – non-invasive treatment required.
- Grade 3: Severe or medically significant but not immediately life-threatening.
- Grade 4: Life-threatening.
- Grade 5: Death.

### **8.3 Definition of malfunctions**

A “malfunction” refers to any problem with the investigational device related broadly to quality, safety or performance, such as damage or malfunction, regardless of whether it arises at the stage of design, delivery, storage or use.

### **8.4 Evaluation of malfunctions**

For malfunctions that occur during use of the investigational device, the following will be recorded as applicable: malfunction name; date and time of occurrence; situation of the malfunction; contributing factors (if any); whether any harm occurred; severity; seriousness; causal relationship with the investigational device; serial number of the investigational device; whether any action was taken for the malfunction (and details if yes); and whether there is a risk of a serious adverse event due to the malfunction.

Malfunctions related to the investigational device include poor image quality or program operational failures when using the pulmonary circulation analysis program. For malfunctions occurring during the trial period, the malfunction name, date and time of occurrence, situation and contributing factors (if any) will be recorded.

If a malfunction is judged to potentially lead to a serious adverse event as defined in Section 8.2.1, the principal investigator will report it in the same manner as a serious adverse event in accordance with Section 8.5.

### **8.5 Reporting procedures for serious adverse events and malfunctions**

If a serious adverse event occurs in relation to the dynamic chest radiography procedure, or if a serious adverse event is suspected to occur due to a malfunction, the principal investigator will, in accordance with the trial’s SOP for handling safety information, report the event to the head of the implementing medical institution and to the coordinating investigator (contact information below), and will also coordinate with the investigational device provider as necessary.

The principal investigator must conduct follow-up investigations for all serious adverse events, and promptly provide the obtained information to the head of the implementing medical institution, the coordinating investigator, principal investigators at other implementing medical institutions, and the investigational device provider.

## **8.6 Information on quality, effectiveness and malfunctions of the investigational device**

The coordinating investigator will collect information on the quality, effectiveness and malfunctions of the investigational device (including domestic and overseas case information, foreign regulatory actions, research reports, etc.) either directly or from the investigational device provider and other sources. The collected information will be handled in accordance with the SOP for handling safety information.

## **8.7 Periodic safety reporting**

The coordinating investigator will conduct periodic reporting in accordance with Article 274-2, Paragraph 4 of the Enforcement Regulations of the Pharmaceuticals and Medical Devices Act, following the SOP for handling safety information, to comprehensively evaluate safety information related to the investigational device.

# **9 Target sample size and study period**

## **9.1 Planned sample size**

A total of 108 cases will be registered (54 cases in the standard initial work-up group and 54 cases in the investigational device group).

Rationale for sample size determination is described in Section 10.1. Based on data from Kyushu University Hospital from January to April 2024, among 17 cases in which pulmonary hypertension was strongly suspected on transthoracic echocardiography and V/Q scintigraphy and right heart catheterisation were performed, the diagnoses were CTEPH in 41% (7/17) and non-CTEPH in 59% (10/17). Assuming a similar 50:50 distribution of CTEPH and non-CTEPH in the planned sample size, at least 10 cases of CTEPH are expected. If fewer than 10 CTEPH cases are included, additional registration will continue until at least 10 CTEPH cases are obtained.

## **9.2 Planned study period**

Planned study period: June 2025 to May 2027.

Planned registration period: June 2025 to February 2027.

## 10 Statistical considerations

### 10.1 Rationale for sample size determination

The diagnostic performance of V/Q scintigraphy is extremely high, with sensitivity and specificity reported as 90–100% and 94–100%, respectively. However, access to V/Q scintigraphy may be delayed and it is not available in many non-expert centres; therefore, adding the pulmonary circulation analysis program to the initial work-up is expected to improve early discrimination of CTEPH.

In the retrospective study conducted at Kyushu University Hospital (Section 1.5), the diagnostic performance of dynamic chest radiography/pulmonary circulation analysis for CTEPH discrimination was high (accuracy 0.92), whereas published data indicate limited diagnostic performance of static chest radiography alone. Based on these data, the expected accuracy for initial discrimination using the standard initial work-up alone is assumed to be approximately 0.705, and the expected accuracy when adding the pulmonary circulation analysis program is assumed to be approximately 0.92 (difference 0.215).

To detect an accuracy difference of 0.215 between the two groups with a two-sided significance level of 5% and 80% power under a 1:1 allocation, the required sample size is calculated as 102 cases (51 per group). Allowing for approximately 5% dropouts or non-evaluable cases, the target sample size was set at 108 cases (54 per group).

### 10.2 Analysis populations

#### 10.2.1 Intention-to-treat (ITT) population

The ITT population is defined as all registered subjects excluding the following:

- Cases judged by the principal investigator to have difficulty in making a clear discrimination diagnosis of CTEPH versus non-CTEPH.
- Cases found after registration to not meet inclusion criteria or to meet exclusion criteria.
- Cases with major non-compliance with Good Clinical Practice (GCP).

#### 10.2.2 Full analysis set (FAS)

The FAS is defined as the ITT population excluding the following:

- Cases in which any of the initial work-up tests (blood tests, static chest radiography, 12-lead ECG, or pulmonary function tests) were not performed, or cases with three or more missing items in blood tests.
- Cases without dynamic chest radiography images, or cases in which the image interpretation committee judges that appropriate dynamic chest radiography images required to perform the pulmonary circulation analysis program are not available (e.g., due to inadequate breath-hold or body motion).

### **10.2.3 Alternative full analysis set for six-region assessment (alt-FAS)**

The alt-FAS is defined as the ITT population excluding the following. This set includes all cases with dynamic chest radiography performed, regardless of group allocation, for the six-region assessment analyses.

- Cases without dynamic chest radiography images, or cases in which the image interpretation committee judges that appropriate dynamic chest radiography images required to perform the pulmonary circulation analysis program are not available (e.g., due to inadequate breath-hold or body motion).
- Cases without perfusion scintigraphy images, or cases in which the image interpretation committee judges that appropriate perfusion scintigraphy images are not available.
- Cases in which the interval between dynamic chest radiography acquisition and perfusion scintigraphy is 15 days or longer.

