**5.7.2 Secondary endpoints**

- Comparison of sensitivity, specificity, positive predictive value and negative predictive value for initial discrimination between CTEPH and non-CTEPH between the group of the standard initial work-up alone versus the device -added group in the ITT population.
- Agreement (kappa coefficient) between the pulmonary circulation analysis program and perfusion scintigraphy regarding the presence of regional perfusion defects in each of six lung regions.

[figure not shown][figure not shown][figure not shown]

| Right                                    | Left                                     |
|------------------------------------------|------------------------------------------|
| Upper:
Perfusion defect
( + / - )  | Upper:
Perfusion defect
( + / - )  |
| Middle:
Perfusion defect
( + / - ) | Middle:
Perfusion defect
( + / - ) |
| Lower:
Perfusion defect
( + / - )  | Lower:
Perfusion defect
( + / - )  |

| Right                                              | Left                                               |
|----------------------------------------------------|----------------------------------------------------|
| Upper:
Segmental perfusion defect
( + / - )  | Upper:
Segmental perfusion defect
( + / - )  |
| Middle:
Segmental perfusion defect
( + / - ) | Middle:
Segmental perfusion defect
( + / - ) |
| Lower:
Segmental perfusion defect
( + / - )  | Lower:
Segmental perfusion defect
( + / - )  |

[figure not shown]

Kappa coefficient for agreement in six area

- Performance evaluation of dynamic chest radiography/pulmonary circulation analysis program for discriminating CTEPH versus non-CTEPH using perfusion scintigraphy as the reference standard: sensitivity, specificity, accuracy, PPV and NPV, in accordance with the STARD 2015 guideline.

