### **10.2.4 Safety analysis set (SAS)**

The SAS is defined as all registered subjects excluding those in whom dynamic chest radiography was not acquired even once.

Analysis populations will be finalised before database lock at a case review meeting. If issues not described here need to be considered for specific cases, the decision will be made at the case review meeting.

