### **13.4 Determination of regional perfusion defects (six-region assessment)**

For the six-region assessment, each lung is divided into upper, middle and lower regions (six regions in total). Each region will be assessed for the presence or absence of a perfusion defect on pulmonary circulation analysis images and on perfusion scintigraphy images.

Pulmonary circulation analysis images will be interpreted by the same five internal medicine physicians as in the intervention group. Perfusion scintigraphy images will be interpreted by three nuclear medicine physicians from CTEPH expert centres. All designated readers will interpret all cases. The final presence/absence of a regional perfusion defect for each region will be determined by majority vote.

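### The alt-FAS is built on the ITT set, so the six-region kappa drops cases with a difficult CTEPH diagnosis although it uses no diagnosis

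*Protocol*

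**What the plan says.** **The set.** Protocol 10.2.3 opens: "The alt-FAS is defined as the ITT population excluding the following". It then states: "This set includes all cases with dynamic chest radiography performed, regardless of group allocation". Three exclusions follow: missing or unsuitable dynamic chest radiography (DCR), missing or unsuitable perfusion scintigraphy, and an interval of 15 days or longer between the two.

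**What the set inherits.** Protocol 10.2.1 removes three kinds of registered subject from the ITT population. The first is: "Cases judged by the principal investigator to have difficulty in making a clear discrimination diagnosis of CTEPH versus non-CTEPH". The others are subjects found ineligible after registration and subjects with major GCP non-compliance.

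**The endpoint.** Protocol 5.7.2 lists as a secondary endpoint: "Agreement (kappa coefficient) between the pulmonary circulation analysis program and perfusion scintigraphy regarding the presence of regional perfusion defects in each of six lung regions". Section 13.4 says how it is read: "Each region will be assessed for the presence or absence of a perfusion defect on pulmonary circulation analysis images and on perfusion scintigraphy images". It adds: "All designated readers will interpret all cases". Sections 5.3.1 and 5.3.2 leave the static radiograph and the ventilation scan out of this reading.

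**Undiagnosable cases.** Section 7.1.5 c) places under non-CTEPH the cases where "An appropriate diagnosis cannot be made or appropriate images/data are not available" and the investigator considers them unsuitable for evaluation.

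**A set with a different base.** Section 10.2.4: "The SAS is defined as all registered subjects excluding those in whom dynamic chest radiography was not acquired even once".

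**The concern.** A rule that drops cases with a difficult final diagnosis has an obvious motive when accuracy is judged against that diagnosis. It has none for agreement between two images of the same lungs. A subject with adequate DCR and adequate perfusion scintigraphy ten days apart supplies everything the kappa needs, and is still removed if the investigator could not settle the diagnosis. The removal is not visible in 10.2.3; it comes in through the reference to the ITT population.

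The selection may also be related to the measurement. The diagnosis is made after scintigraphy, and the first CTEPH criterion in 7.1.5 is a segmental or multiple subsegmental perfusion defect. Equivocal perfusion images are therefore one route to an unclear diagnosis, and two modalities may agree less on such images. At stake is whether the reported agreement describes all patients with usable image pairs or only those whose diagnosis was clear.

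**Working it through.** **1. Membership under each sentence.** Take a registered, eligible, GCP-compliant subject with adequate DCR and scintigraphy within 14 days and a diagnosis judged difficult.

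- Under the opening sentence of 10.2.3 with 10.2.1, the subject is out.
- Under the next sentence of 10.2.3, read literally, the subject is in.
- Under the three image and interval exclusions, there is no reason to drop the subject.
- Under 5.3.1, 5.3.2, 5.7.2 and 13.4, the endpoint uses no final diagnosis.

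No other section restores the subject to the kappa analysis.

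**2. The protocol's own agreement figures (section 1.5).** Stated: agreement 0.90 [0.79–0.95], kappa 0.79, 50 patients. Table 2 gives V/Q 32 positive and 18 negative, and device 31 positive and 19 negative. With 45/50 agreeing, the cells must be 29 both positive, 2 device only, 3 V/Q only, 16 both negative.

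- Expected agreement = (32×31 + 18×19)/50² = 1334/2500 = 0.5336
- Kappa = (0.90 − 0.5336)/(1 − 0.5336) = 0.786, which rounds to the stated 0.79.

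So 0.90 is a patient-level figure. The interval agrees: a Wilson interval for 45/50 is about 0.79 to 0.96, whereas 90% of 300 regions would give about 0.86 to 0.93. The protocol gives no regional agreement figure.

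**3. Regional illustration (all inputs assumed).** Let clear cases agree in 90% of regions, with half of regions positive on each modality. Expected agreement is 0.5, so kappa = 2×agreement − 1 = 0.80. Let a share f of cases be unclear, with agreement a and the same margins. The amount by which dropping them raises kappa is 2f(0.90 − a).

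| Unclear share f | All-case kappa, a = 0.50 | All-case kappa, a = 0.70 | Shift from 0.80 |
|---|---|---|---|
| 5% | 0.76 | 0.78 | 0.02 to 0.04 |
| 10% | 0.72 | 0.76 | 0.04 to 0.08 |
| 15% | 0.68 | 0.74 | 0.06 to 0.12 |

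At a = 0.90 the shift is zero; above that it reverses. For one region and n = 103 (about 108×0.95), SE ≈ √(0.90×0.10/103)/0.5 = 0.059, rising to about 0.07 at the lower agreements. At 5% unclear the shift is 0.3 to 0.7 SE.

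**4. Patient-level cross-check.** Mix the table in step 2 with unclear cases at a defect prevalence of 0.30 to 0.64.

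| Unclear share | a = 0.50 | a = 0.70 | a = 0.90 |
|---|---|---|---|
| 6/108 = 5.6% | 0.74 | 0.76 to 0.77 | 0.79 |
| 10% | 0.70 to 0.71 | 0.74 to 0.75 | 0.79 |
| 20% | 0.61 to 0.63 | 0.70 to 0.72 | 0.79 to 0.80 |

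Against 0.786, the overstatement is about 0 to 0.05 at 5.6% and up to about 0.17 at 20%.

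**5. Which share is plausible.** The only related figure is the allowance of about 5% in 10.1 (102 raised to 108), which covers dropouts and non-evaluable cases together. Unclear diagnoses can be only part of it. It is a planning figure, not an observed rate.

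**The case against.** - **The sentence about all cases is a clarification.** A reader might infer that 10.2.3 holds two membership rules in flat contradiction. The text does not support that. The sentence goes on to its purpose, the six-region analyses, and most naturally says that both reading groups contribute. Taken literally it would also clash with the image exclusions listed directly below it. What stands is narrower: its wording does not match the ITT base.
- **Inflation is not shown.** A reader might infer that kappa will come out too high. CTEPH also requires organised thrombi on angiography and haemodynamic criteria at catheterisation (7.1.5). A diagnosis can be unclear for those reasons while the perfusion images are plain, and then the exclusion need not move kappa. This objection stands.
- **The anchor is not regional.** The 0.90 and 0.79 in section 1.5 are patient-level and compare the device with V/Q scintigraphy, while the six-region reading ignores ventilation. They cannot be read as the regional level in clear cases. This stands too, and the figures above are illustrations only.
- **Starting from all registered subjects goes too far.** With only the image exclusions, ineligible subjects (for example those with chest devices or lung resection, section 3.2) and major GCP non-compliance would return. Nothing in this point justifies that.
- **The route to reading.** Section 5.6 stratifies allocation by final diagnosis and gives reading IDs to allocated cases, so an undiagnosed case might never be read. Section 7.1.5 c) largely answers this with a non-CTEPH label; 5.6 has analysis images made for all cases, and 13.4 has all cases read.
- **It follows from the ITT definition.** True. Removing the diagnostic exclusion from 10.2.1 would settle this as well. As long as that exclusion stays for the accuracy endpoint, the alt-FAS needs its own base.

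**Conclusion.** The point holds as a needless selection in a secondary endpoint. Section 10.2.3 passes on to the six-region kappa an exclusion for diagnostic difficulty that the endpoint does not need, and that depends partly on one of the two image sets being compared. An upward bias is possible, but the protocol gives neither the number of unclear cases nor their agreement, so size and direction stay open. If 5% of cases are unclear and agree in 50 to 70% of regions, against an assumed 90% in clear cases, the shift is 0.02 to 0.04, below one standard error. It is nil if they agree as well as clear cases. Shifts of 0.1 or more need shares of unclear cases well above the planning allowance together with poor agreement, and the documents give neither. The primary endpoint is not touched by this point.

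**What to change.** In 10.2.3, define the alt-FAS as registered subjects in either reading group, regardless of final diagnosis or diagnostic certainty, with adequate DCR and adequate perfusion scintigraphy no more than 14 days apart. Keep the three image and interval exclusions, and keep the ITT exclusions for ineligibility and major GCP non-compliance. Reword the sentence about all cases to say that both reading groups contribute. Report the ITT-based kappa as a sensitivity analysis, with the number of cases that separates the two sets.

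Reconcile 7.1.5 c) with 10.2.1: one labels undiagnosable cases non-CTEPH, the other removes difficult diagnoses from the analysis. State that such cases still receive a reading ID for the six-region reading.

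The cost is a short edit, a few more cases in the analysis and possibly a slightly lower kappa. Subjects need no additional imaging.
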